## Abstract

**Background:**

Heavy metals present in the environment, including lead, cadmium, and mercury, pose significant health risks to pregnant women and fetal development through food, water, and air contamination. Exposure to these metals has been linked to miscarriage, low birth weight (LBW), preterm birth, and developmental issues in children. The mechanism of oxidative stress, characterized by increased 8-hydroxy-2’-deoxyguanosine (8-OHdG) and malondialdehyde (MDA) levels, contributes to DNA damage, genomic instability, and adverse pregnancy outcomes. Additionally, DNA methylation changes induced by metal exposure may further exacerbate these risks. Certain micronutrients play a crucial role in heavy metal detoxification, and *Moringa oleifera*, a locally available plant rich in antioxidants and chelating compounds**,** has demonstrated protective effects against mercury (Hg), lead (Pb), and cadmium (Cd) toxicity in experimental studies. However, intervention studies on pregnant women remain scarce.

**Objective:**

The objective of this study was to evaluate the effect of *M. oleifera* supplementation in reducing heavy metal toxicity and oxidative stress biomarkers, 8-OHdG and MDA, in pregnant women exposed to high levels of heavy metals.

**Methods:**

A quasi-experimental, nonrandomized pre-post test design is used. Pregnant women with elevated heavy metal levels, identified through initial screening, will be included in the intervention group, receiving *M. oleifera* supplementation for 2 months. The control group will consist of women from similar geographical regions who will not receive the intervention. Primary outcomes will include changes in heavy metal concentrations, measured using inductively coupled plasma mass spectrometry (ICP-MS). Secondary outcomes will focus on reductions in oxidative stress biomarkers, measured via enzyme-linked immunosorbent assay (ELISA). Statistical analyses, including analysis of covariance (ANCOVA), will be used to adjust for baseline differences between the groups.

**Results:**

A total of 26 mothers for each group have participated. As of February 2025, the laboratory analyses have been ongoing, and the result is expected to be published at the end of 2025. The protocol anticipates that the intervention group will show a significant reduction in both heavy metal levels and oxidative stress biomarkers compared to the control group, suggesting the potential efficacy of *M. oleifera* in detoxifying heavy metals and reducing oxidative stress.

**Conclusions:**

This study is expected to provide preliminary evidence on the potential effectiveness and safety of *M. oleifera* supplementation for reducing heavy metal toxicity and oxidative stress in pregnant women.

## Introduction

Heavy metals such as cadmium (Cd), mercury (Hg), and lead (Pb) exist in water, air, and food, contributing to cumulative exposure in humans [1,2]. According to the World Health Organization (WHO), Pb exposure alone is responsible for nearly 1 million deaths annually and more than 21 million disability-adjusted life years (DALYs) lost, with more than 95% of this burden occurring in low- and middle-income countries (LMICs) [3]. Prenatal exposure to Pb and other heavy metals is particularly harmful as it has been linked to miscarriage, preterm birth, low birth weight (LBW), and developmental problems in children [4-6]. Studies have shown that no level of lead exposure is considered safe during pregnancy, and even low-dose exposures can disrupt fetal development. These risks highlight the urgent need for public health interventions targeting environmental metal exposures in vulnerable populations, especially among pregnant women in LMICs where monitoring and remediation remain limited.

In Makassar, Indonesia, 717, 347, and 816 LBW cases were reported in 2021, 2022, and 2023, respectively. Preliminary investigation also revealed significantly elevated levels of blood Pb (1.35–101.00 μg/L) and Cd (0.55–17.00 μg/L), exceeding reference values in various countries [7]. For context, the US Centers for Disease Control and Prevention (CDC) considers blood Pb levels above 5 μg/dL (50 μg/L) as elevated in adults [8-10], while the WHO identifies Cd concentrations exceeding 1 μg/L in blood as potentially toxic. These findings highlight a concerning level of environmental exposure during pregnancy. Although specific to Makassar, such elevated exposures reflect broader environmental health challenges in urban Indonesia and Southeast Asia, where industrial emissions, traffic pollution, and inadequate regulation contribute to rising heavy metal contamination.

One key mechanism underlying the heavy metal toxicity is oxidative stress, which causes damage to lipids, proteins, and DNA. Biomarkers such as malondialdehyde (MDA) and 8-hydroxy-2’-deoxyguanosine (8-OHdG) reflect oxidative damage and are commonly elevated in metal-exposed individuals  [7-9]. Additionally, heavy metals can disrupt DNA methylation [10], an epigenetic process critical for normal fetal development, thereby contributing to adverse pregnancy outcomes  [11-13]. Heavy metals such as Pb, Cd, and Hg exert toxic effects partly through the generation of reactive oxygen species (ROS), leading to oxidative stress [14]. This imbalance between ROS and antioxidant defenses causes damage to cellular lipids, proteins, and DNA, as reflected by increased levels of oxidative stress biomarkers such as 8-OHdG and MDA [15,16]. These molecular injuries are particularly harmful during pregnancy as they disrupt placental development and fetal growth processes [17,18]. Studies have shown that oxidative stress plays a central role in the pathogenesis of adverse pregnancy outcomes [19], including preeclampsia [20], miscarriage [21], LBW [22], and preterm birth [23]. A previous study by Zinia et al [24] indicated that high maternal blood Cd levels (0.62 μg/L in early pregnancy and 0.70 μg/L in late pregnancy), Pb levels (early pregnancy 0.74 vs late pregnancy 0.70 μg/dL), and Hg levels (early pregnancy 2.37 vs late pregnancy 1.95 μg/L) were inversely associated with birth weight.

Although certain micronutrients such as zinc and cysteine may assist in the detoxification of heavy metals [25], their use as targeted interventions remains inconsistent and often inaccessible to at-risk populations. Therefore, *Moringa oleifera* has emerged as a promising, locally available resource. Moringa contains flavonoids, phenolic acids, glucosinolates, and phytates and exhibits antioxidant and metal-chelating properties that can mitigate the toxic effects of heavy metals [26,27]. These compounds have been shown in in vitro and in vivo studies to counteract oxidative stress and inflammation induced by toxicants, including heavy metals.

Beyond laboratory studies, there is growing evidence of moringa’s nutritional and therapeutic effects in humans. Moringa leaf supplementation has shown improvements in hemoglobin levels in children with iron deficiency anemia and increased breast milk production in postpartum women [28]. In a clinical trial, moringa leaf powder (0.5 g/d) led to significant reductions in body weight, blood pressure, and lipid profiles in overweight individuals with hyperlipidemia [29]. In pregnant women, moringa has emerged as a beneficial supplement, particularly in enhancing maternal and neonatal health. A study in southern Ethiopia found that the consumption of moringa was associated with an increase in birth weight by approximately 115.77 g, suggesting its potential role in improving neonatal outcomes [30]. Moringa leaves are rich in iron, which is crucial for preventing anemia during pregnancy. A study in Karachi reported that pregnant women consuming moringa leaf powder showed hemoglobin levels of 9.09 g/dL in the third trimester, indicating a potential benefit in managing anemia [31]. No contraindications for moringa use during pregnancy were reported in the reviewed studies, suggesting it is generally safe for consumption [32].

Although moringa grows abundantly in many regions of Indonesia, particularly in Makassar, it is typically consumed sporadically as a vegetable, with unmeasured doses and limited awareness of its therapeutic potential. In other areas, such as Java, consumption is even more limited. These factors underscore the need for a standardized, supplement-based intervention to realize public health benefits of moringa. Despite the well-documented risks of heavy metal exposure during pregnancy, interventional studies remain scarce, particularly in Indonesia. To date, there has been no clinical trial examining the efficacy of moringa in the detoxification of heavy metals among pregnant women. In addition, most existing research is observational and lacks an evaluation of strategies to reduce maternal metal levels or oxidative damage. This study seeks to address this gap by investigating the effect of standardized *M. oleifera* supplementation on heavy metal level and oxidative stress reduction in pregnant women. We hypothesize that pregnant women receiving *M. oleifera* supplementation will have significantly lower blood heavy metal concentrations and oxidative stress biomarkers than before receiving.

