The required sample size was calculated using an estimated effect size (Cohen *d*) of 0.42, derived from a previous intervention study in South Sulawesi, which assessed the effects of *M. oleifera* supplementation on oxidative stress biomarkers in pregnant women exposed to passive smoking [37]. The study reported a mean difference in 8-OHdG levels between treatment groups of approximately 12.96 ng/mL with a pooled SD of ~30.68 ng/mL, yielding a moderate effect size. Using a 1-sided test with *α*=.05 and 80% power, the minimum required sample size is 37 participants per group. To account for an anticipated 20% dropout rate, the sample size was increased to 44 participants per group, yielding a total of 88 participants.

Approximately 200 pregnant women attending routine antenatal care (ANC) visits at the community health centers were sequentially approached and invited to participate in the study. They were first interviewed to determine eligibility based on inclusion and exclusion criteria. Those meeting the criteria were provided with detailed information about the study and asked to provide written informed consent. Following consent, a blood sample was collected to assess baseline levels of heavy metals.

Only participants with elevated levels above reference thresholds were considered eligible for inclusion in the intervention phase. For the intervention group, eligible participants were contacted and provided with *M. oleifera* supplements along with instructions for daily consumption over a 2-month period. They were informed that a follow-up blood collection would occur at the end of the supplementation period during a routine visit.

For comparison, the control group was recruited from a different health center in a separate subdistrict administrative unit that did not receive moringa supplementation. This approach minimized contamination between groups and allowed for feasible implementation of the intervention. Follow-up blood sampling was also conducted after 2 months, aligned with their next scheduled antenatal visit, but without providing moringa supplementation.

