### Data Analysis

All analyses will be conducted using the R statistical software (latest version). Data entry and cleaning will be conducted by trained staff using a double-entry verification. For 24-hour food recall data, participants will be asked to estimate portion sizes using visual aids, and data will be reviewed during collection for completeness and clarity. For the FFQ, if participants leave implausible answers (eg, extremely high frequency), the data will be reviewed and clarified during the interview or excluded from analysis after documentation. Implausible intake frequency will be cross-checked with interview notes and food recall summaries to determine plausibility. An intention-to-treat (ITT) analysis will be performed to preserve the benefits of initial group allocation. For missing or partial responses, multiple imputation will be considered for covariates in the adjusted models. For missing outcome data at follow-up, last observation carried forward (LOCF) will be used when feasible. Sensitivity analyses will be conducted to assess the robustness of findings under different missing data assumptions. Outliers will not be automatically excluded unless clear reporting errors are confirmed. Outliers in biomarker measurement will be identified using the interquartile range method and retained unless proven to result from analytic error or sample contamination. All statistical analyses will be conducted with and without outliers to assess the robustness of the results.

Descriptive statistics will summarize participant characteristics. All continuous variables, including heavy metal concentrations and biomarker levels, will be checked for normality before analysis. In the case of non-normal distributions, appropriate data transformations (eg, log transformation) will be applied. If normality cannot be achieved, nonparametric tests (eg, Mann–Whitney *U* or Wilcoxon signed-rank test) will be used as alternatives. Analysis of group differences (pre- and postintervention). For each group, analysis will be conducted using the paired *t* test or Wilcoxon signed-rank test, depending on data distribution, to assess changes in heavy metals, MDA, and 8-OHdG levels before and after intervention. The significance level (alpha) will be set at .05, and all tests will be one-tailed.

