### Expected Outcomes

#### Reduction in Blood Heavy Metal Levels

The primary outcome of this study is the reduction in blood Pb/Cd/Hg level. The hypothesis is that supplementation with *M. oleifera* will result in a reduction in the blood levels of heavy metals in pregnant women compared to those in the control group. Hence, the expected results are as follows: (1) A measurable decrease in the blood Pb/Cd/Hg concentration will be observed in the group receiving *M. oleifera* supplementation for 2 months. (2) The intervention group is expected to show a greater reduction in blood heavy metal levels than the control group, based on pre- and post-test analyses.

Scientific implications expected are that the result would provide evidence that *M. oleifera* has the potential to detoxify, thereby demonstrating that it is a safe and effective approach to reducing heavy metal accumulation in expectant mothers, who are at a higher risk of exposure to environmental pollutants.

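### The Introduction's hypothesis and one reading of the within-arm tests treat a before-after fall as efficacy, although selection on a high baseline makes falling metal levels likely without treatment

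*Protocol article*

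**What the plan says.** The protocol article states its hypothesis in two ways.

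- **Before versus after.** The Introduction expects "significantly lower blood heavy metal concentrations and oxidative stress biomarkers than before receiving". Data Analysis plans a paired t test or Wilcoxon signed-rank test in each group "to assess changes in heavy metals, MDA, and 8-OHdG levels before and after intervention", and adds: "The significance level (alpha) will be set at .05, and all tests will be one-tailed". Under Reduction in Blood Heavy Metal Levels, expected result (1) is: "A measurable decrease in the blood Pb/Cd/Hg concentration will be observed in the group receiving" the supplement. Under Reduction in 8-OHdG and MDA Concentrations, expected result (1) goes further and takes a significant fall in the treated arm as a sign of protection.
- **Against control.** The hypothesis under Reduction in Blood Heavy Metal Levels is that supplementation "will result in a reduction in the blood levels of heavy metals in pregnant women compared to those in the control group". The 8-OHdG and MDA hypothesis is also set against control. Data Analysis plans difference-in-differences, and ANCOVA with baseline levels as covariates.

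On selection, Participant Recruitment requires at least one of Hg, Pb or Cd above its reference value. The blood drawn after consent gives the baseline metal levels, and only women above threshold continue. No second pre-treatment sample is described.

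**The concern.** The two hypotheses are different claims, and one can be true while the other is false. The before-after version is not protected against regression to the mean. A woman who qualifies on one high reading will, on average, read lower next time whatever she takes. With a one-tailed test in the direction of a fall, that artefact counts as success, so the Introduction's hypothesis could be confirmed with an inert capsule. The article does not say which of the planned tests decides efficacy, so a reader may take the easier within-arm result as the answer.

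**Working it through.** **1. The plan's own figure.** Participant Recruitment gives "80% power, the minimum required sample size is 37 participants per group", one-sided α = .05, with d from a "mean difference in 8-OHdG levels between treatment groups of approximately 12.96 ng/mL with a pooled SD of ~30.68 ng/mL". Check: 12.96/30.68 = 0.42.

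- Paired or one-sample formula: ((1.645 + 0.842)/0.42)² = 35.05, so 36. With the noncentral t it is 37, the stated figure.
- Two-group formula: 2 × 35.05 = 70.1, so 71 per group. The stated figure does not reproduce this way.

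So 37 matches a within-arm test, although its effect size is a difference between groups. One-sided power of an unadjusted two-group test at d = 0.42 is about 45% with 26 per group (the number reported as having participated), 56% with 37, 63% with 44 and 74% with 59.

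**2. Expected fall with no treatment effect and no drift.** These inputs are not in the documents and are assumed: a normal (log) scale, the same relative cut-off for each metal, baseline/follow-up correlation ρ = 0.6–0.8, inter-metal correlation 0–0.3, and half or three quarters of women qualifying on any one of three metals. n = 26 comes from Results.

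For uncorrelated metals there is a closed form. The cut-off c satisfies Φ(c)³ = 1 − f, where f is the fraction qualifying. The mean baseline excess per metal is φ(c)Φ(c)²/f, and the expected fall is (1 − ρ) times that.

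- f = 0.50: Φ(c) = 0.794, c = 0.82, excess = 0.285 × 0.630/0.50 = 0.36 SD. The fall is 0.14 SD (ρ = 0.6) to 0.07 SD (ρ = 0.8).
- f = 0.75: Φ(c) = 0.630, c = 0.33, excess = 0.378 × 0.397/0.75 = 0.20 SD. The fall is 0.08 to 0.04 SD.

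Positive correlation between metals makes the excess larger.

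**3. False-positive rate of the one-tailed .05 paired test.** Simulation under the same assumptions gives the following; repeat runs move the figures by a point or so.

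| Women qualifying | Per metal |
|---|---|
| Half | about 13–31% |
| Three quarters | about 10–15% |

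At least one of the three metals is falsely significant in about 26–61% of null trials over both rows. The reference for that figure is not 5%: three independent tests at .05 give 1 − 0.95³ = 14%.

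**4. The between-group contrast under the same null.** In a simpler model with selection on the tested metal, a difference-in-differences test with 26 per arm stays near 5% when both arms are selected alike. If the treated arm is the top 26% (52 of about 200 approached, as an illustration) and the control arm the top 50%, it rises to 10–16% for ρ = 0.9 to 0.7.

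**5. Gestational change cited in the Introduction.** Hg: (1.95 − 2.37)/2.37 = −18%. Pb: (0.70 − 0.74)/0.74 = −5%. Cd: (0.70 − 0.62)/0.62 = +13%.

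**The case against.** The strongest reply is that the plan already has a control group, difference-in-differences and ANCOVA, and calls its findings preliminary and hypothesis-generating. That stands in part. A reader might infer that efficacy rests on the paired tests alone, and the documents do not support this. What remains is a misaligned hypothesis, one explicit efficacy reading of a within-arm result, and no stated priority among the tests.

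Four other stronger readings also fail.

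- **Drift makes a fall expected for every metal.** The background figures include "Hg levels (early pregnancy 2.37 vs late pregnancy 1.95" μg/L, a fall, but Cd rises. They compare early with late pregnancy, not enrolment at weeks 20–32 with 8 weeks later. They show only that levels can move either way without moringa.
- **The false-positive rate is 36–59% (half qualifying) or 16–27% (three quarters).** Those rates arise if every woman is selected on the metal being tested. The eligibility rule admits her on any of three, so the tested metal is only partly selected.
- **Regression to the mean applies equally to 8-OHdG and MDA.** Nobody is selected on them. It reaches them only through their correlation with the metals.
- **The plan compares one arm's p-value with the other's.** It runs paired tests in each arm but nowhere draws that inference.

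**Conclusion.** The concern holds as an inconsistency with a measurable consequence. The Introduction's success criterion is contradicted by the control-based hypotheses and the planned between-group analysis. For the metals, it would be met by chance well above the nominal 5%: about 10–31% per metal across the scenarios. The size rests on the assumed correlations and qualifying fraction, none of which the documents give. The direction does not, because selection on a single high reading lowers the expected second reading whenever the correlation is below 1. For 8-OHdG and MDA the objection is simpler: an uncontrolled before-after change cannot be credited to the supplement.

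**What to change.** - Rewrite the Introduction's hypothesis as a greater reduction than in the control group, matching Expected Outcomes.
- In Data Analysis, name the baseline-adjusted between-group contrast already planned there as the efficacy test.
- Label the within-arm paired results descriptive.
- Reword expected result (1) for the metals, and expected result (1) for 8-OHdG and MDA, so that a within-arm fall is not read as evidence of effect.

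**Cost.** The easier within-arm claim is lost, and the change goes beyond wording. The sample-size basis must be restated: an unadjusted two-group test at d = 0.42, one-sided .05 and 80% power needs 71 per group, and 26 per group gives about 45% power. ANCOVA would do better, by an amount that depends on a baseline/follow-up correlation the article does not give.

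**Limit.** The fix does not remove bias from unequal selection. Study Design says that women found high at first screening were put in the intervention group to avoid delay. If the two arms were selected differently, the between-group contrast also carries some regression to the mean (step 4).

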## Methods

### Study Design

This study is an ongoing quasi-experimental investigation that uses a nonrandomized pre-post test methodology. Expectant mothers were divided into 2 cohorts, one receiving an intervention and the other serving as a control. This study applied a nonrandomized pre-post test design due to practical considerations related to (1) practical management, (2) geographical differences, and (3) time constraints.

First, practical management considers that managing the study is easier when specific locations are designated for the intervention group and other locations for the control group. This approach ensures that the intervention (*M. oleifera* supplementation) can be efficiently delivered and monitored in each location without the complexity of randomizing participants across multiple sites. Furthermore, grouping participants by location helps streamline logistical operations such as monitoring compliance and ensuring consistent follow-up over the course of the intervention period.

Second, although the geographical settings of the intervention and control groups may differ, they were comparable in terms of demographic characteristics and environmental conditions. This allowed us to evaluate the effects of moringa supplementation in different geographical settings while maintaining comparability between groups. In addition, by focusing on distinct locations for intervention and control, we ensure better resource allocation and minimize the logistical challenges that would arise from attempting to randomize participants across a broader region.

Third, time was considered a constraint due to limitation in the laboratory. We could not receive heavy metal analysis results from the initial screening at the same time for all participants. Therefore, women with high levels of heavy metals at the first screening were included in the intervention group to avoid delays. This ensures that these participants can begin the 2-month intervention with *M. oleifera* as soon as possible after obtaining the result, considering the limited research timeframe. Furthermore, because we limited the overall time for the study, randomizing participants could cause delays in implementing the intervention and complicate the process of ensuring that those with high levels of heavy metals receive timely treatment.

A nonrandomized approach allows for a more timely intervention, while still enabling an effective comparison between the intervention and control groups. Statistical methods will be used to control for baseline disparities and account for potential differences between the groups.

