### Biomarker Analysis

#### Heavy Metal Analysis

The measurement was conducted to determine Hg, Pb, and Cd levels in the blood of pregnant women during the second or third trimester. Heavy metals were analyzed using inductively coupled plasma mass spectrometry (ICP-MS) (Thermo Fisher Scientific, Bremen, Germany) and performed in micrograms per liter. To ensure analytical accuracy and method validation, we used certified reference materials (CRM BCR®-636, lyophilized human blood, Joint Research Center-JRC, European Commission) as a quality control standard. For quality assurance and quality control (QA/QC), calibration curves were generated using multielement standard solutions of known concentrations. Blank samples were included in each analytical batch to monitor contamination.

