#### Oxidative Stress Analysis

In this study, 8 OHdG and MDA are used as biomarkers of oxidative stress because they capture two complementary pathways: DNA oxidative damage and lipid peroxidation, respectively. Both markers have been validated in pregnant populations exposed to heavy metals such as Pb, Cd, and Hg. Alternative enzymatic antioxidants (eg, glutathione peroxidase, catalase) require immediate enzyme activity preservation, which cannot be guaranteed under our field conditions; 8 OHdG and MDA, by contrast, remain stable in frozen plasma and are therefore better suited to the study’s logistics.

Plasma concentrations of MDA (nmol mL⁻¹) will be quantified in duplicate using a commercially available ELISA kit (Thermo Fisher Scientific, Bremen, Germany). 8 OHdG (ng mL⁻¹) will be measured in duplicate with a validated ELISA kit (Bioassay Technology Lab, Shanghai Korain Biotech Co. Ltd). For each assay run, an 8-point standard curve, reagent blanks, and low-/high-quality control samples will be included. Concentrations will be derived from the standard curves using a 4-parameter logistic model, and any sample with a coefficient of variation > 10 % on duplicate readings will be reassayed. Laboratory technicians will be blinded to group allocation to minimize measurement bias.

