## Results

Overview

The study was funded in 2024 and data collection began in July 2024. A total of 26 mothers in each group have participated. As of February 2025, the laboratory analysis is ongoing for the second step. We expect the results to be published at the end of 2025.

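### Blood metals are assayed at screening for baseline and later for follow-up, so assay-run differences can enter the before-after tests, and the arm comparison if the arms fall in different runs.

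*Protocol article*

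**What the plan says.** **Timing of the metal assays.** Study Design reports that "We could not receive heavy metal analysis results from the initial screening at the same time for all participants" and that, in consequence, "women with high levels of heavy metals at the first screening were included in the intervention group to avoid delays". Participant Recruitment makes the baseline result a gate: "Only participants with elevated levels above reference thresholds were considered eligible for inclusion in the intervention phase". The same section assigns arm by health center, with controls drawn from a separate subdistrict.

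**Timing of the other biomarkers.** Data Collection places baseline measurement of metals, 8-OHdG and MDA at enrollment and has the same biomarkers reassessed after 8 weeks. It also says that plasma for 8-OHdG and MDA is held at −80 °C until analysis. Oxidative Stress Analysis says that these two markers "remain stable in frozen plasma and are therefore better suited to the study’s logistics". Results adds: "As of February 2025, the laboratory analysis is ongoing for the second step". That second step is not defined.

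**Controls.** Heavy Metal Analysis lists calibration curves, a certified human-blood reference material and blanks: "Blank samples were included in each analytical batch to monitor contamination". Oxidative Stress Analysis lists a standard curve, blanks and low and high controls in every run, duplicate readings with reassay above a 10% coefficient of variation, and technicians blinded to group.

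**Analyses.** Data Analysis plans paired tests in each group "to assess changes in heavy metals, MDA, and 8-OHdG levels before and after intervention", with all tests one-tailed at .05. Between groups it plans DiD and ANCOVA. The ANCOVA covariates, given as examples, do not include assay run or plate.

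**The concern.** A before-after change is a difference between two laboratory readings. If all baseline readings come from one set of runs and all follow-up readings from a later set, a systematic difference between the sets looks the same as a change in the women. A downward shift would count as a moringa effect in a one-tailed test; an upward shift would hide one.

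This matters because the hypothesis in the Introduction is itself before-after (lower values than before supplementation), and the first expected result for the metals and for the oxidative markers is a fall within the intervention group. A control group protects the DiD contrast from a shift that both arms share. It does not protect the within-group tests, and it does not protect DiD if the arms were measured in different runs.

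**Working it through.** The plan states no run-to-run variation, so there is no figure of its own to reproduce. The check has two parts.

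**1. What the text fixes about runs**

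- *Metals, time point.* The baseline result must be known before a woman enters the intervention phase, so that assay precedes the 8-week blood draw. Baseline and follow-up readings therefore come from different occasions. The quality-control text confirms more than one batch.
- *Metals, arm.* Early high results went to the intervention group, which links order of results to arm. Arm is also set by health center, and both arms are screened and resampled. No section says which arm was in which run.
- *8-OHdG and MDA.* The staggered results concern metals only. Measurement at enrollment followed by reassessment can be read as two separate assays; storage until analysis is equally compatible with one paired assay. Neither is stated.

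**2. How a run difference would act**

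Assumptions, none from the documents: log scale; SD of a woman's log change s = 0.25 (0.40 as an alternative); between-run SD r = 0.03, 0.05 or 0.10, about 3%, 5% or 10%; no treatment effect. From the documents: n = 26 per group (Results) and one-tailed .05.

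- SE(DiD) = s√(2/n) = 0.25 × √(2/26) = 0.0693
- SE(paired) = s/√n = 0.25/√26 = 0.0490
- Run variance V added to DiD: 4r²/k, when each of the four arm-by-time cells has its own k runs with women spread evenly over them
- Run variance V added to DiD when only the baseline runs differ by arm: 2r² (k = 1)
- Run variance V added to a paired test: 2r²/k
- False-positive rate = 1 − Φ(1.645 × SE / √(SE² + V))

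Example, r = 0.05, k = 1: V = 4 × 0.0025 = 0.0100; √(0.0693² + 0.0100) = 0.1217; 1.645 × 0.0693/0.1217 = 0.937; rate = 17%.

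| Layout | r = 3% | r = 5% | r = 10% |
|---|---|---|---|
| DiD, one distinct run per cell, s = 0.25 | 11% | 17% | 29% |
| DiD, three runs per cell, s = 0.25 | 7% | 10% | 20% |
| DiD, one baseline run per arm, follow-up shared, s = 0.25 | 8% | 12% | 23% |
| DiD, one distinct run per cell, s = 0.40 | 7% | 11% | 21% |
| DiD, arms share runs at each time point | 5% | 5% | 5% |

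The within-group paired test has the same rates as the matching DiD rows (11%, 17%, 29% with one run per time point; 7%, 10%, 20% with three), because V and SE² are both halved. Sharing runs between arms does not help it.

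A separate check used a fixed downward shift at follow-up of 0.3 SD of the change, with 37 per group. If both arms have the shift, the paired test rejects in 56% of simulated trials and the between-arm test in 5%. If only one arm has it, the between-arm test rejects in 35%.

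**The case against.** The strongest reply is that this is laboratory detail. A journal article may leave plate layout, run allocation and a run term to a laboratory manual or an analysis plan not shown, and the covariate list is only illustrative. That stands against treating the missing run term as an error in itself. It does not dispose of the point for metals, because the article itself describes baseline and follow-up assay on different occasions and plans paired tests that take the difference at face value.

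The stated controls are real. Calibration, reference material, blanks and per-run curves limit run differences; how much remains is unknown. Blinded technicians do not help here, since a run shift needs no knowledge of group.

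A reader might infer three stronger things that the documents do not support:

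- *That all baseline samples were assayed in staggered batches.* This is shown for metals only.
- *That the second step in Results is the follow-up assay.* It could equally be the ELISA phase. The argument for metals does not need it.
- *That the arms were measured in different runs, so the between-group result is biased.* No section says so. The rates of 11% to 29% also assume a single run in each cell, which fits poorly with staggered baseline batches; with three runs they fall to 7% to 20%.

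**Conclusion.** The concern holds in a limited form. For blood metals, the primary outcome, time point is tied to assay run as the protocol is written, so residual run differences enter the within-group before-after tests. They enter DiD and ANCOVA only if the arms fall in different runs, which is possible but not shown. For 8-OHdG and MDA it is an avoidable risk, not a demonstrated fault.

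The size is illustrative. The rates rest on an assumed between-run SD and SD of change, and on the number of runs per cell. For the between-group test they run from no inflation (arms sharing runs) to 29% (one distinct run per cell and a 10% between-run SD). Adding women does not shrink the error unless they are spread over more runs.

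**What to change.** 1. **Oxidative Stress Analysis.** State that each woman's baseline and follow-up plasma are assayed on the same ELISA plate, with arms balanced across plates, and include plate in the 8-OHdG and MDA models.
2. **Heavy Metal Analysis.** Assay follow-up blood from both arms in the same ICP-MS runs, record the run identifier of every reading, and report a sensitivity analysis correcting each run to its own reference-material recovery. Re-run stored baseline blood only as a further sensitivity analysis: Data Collection keeps the blood at 2–8 °C, so re-assay swaps a run difference for a storage-time difference.
3. **Data Analysis and Expected Outcomes.** Base the moringa effect on the between-group comparison. Present within-group changes measured across different runs as description only.

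**Cost.** Mainly plate planning. On an assumed 96-well plate with 16 standard, 2 blank and 4 control wells, 96 − 22 = 74 wells hold 37 samples in duplicate, or 18 complete pairs. For each marker, the 52 women (104 samples) need 3 plates whether or not pairs are kept together (104/37 = 2.8; 52/18 = 2.9). If baseline plasma has already been assayed, a few extra kits are needed. For metals the required addition is one sensitivity analysis. No new participants, visits or blood draws are needed.
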